## 8 TRIAL TIMELINE AND PROCEDURES

### 8.1 Trial timeline

[figure not shown]

## 8.2 Patient/caregiver schedule of assessments

|                                                                                                                                                     |                                                                                                                                                                                                                                                                                                                                                                                                                                                 |                                                                                       |
|-----------------------------------------------------------------------------------------------------------------------------------------------------|-------------------------------------------------------------------------------------------------------------------------------------------------------------------------------------------------------------------------------------------------------------------------------------------------------------------------------------------------------------------------------------------------------------------------------------------------|---------------------------------------------------------------------------------------|
| Information relating to study sent via letter and study team contact family by phone to ask if interested in study and to provide more information. |                                                                                                                                                                                                                                                                                                                                                                                                                                                 |                                                                                       |
| Consent                                                                                                                                             | [figure not shown]                                                                                                                                                                                                                                                                                                                                                             |                                                                                       |
| Baseline survey                                                                                                                                     | [figure not shown]                                                                                                                                                                                                                                                                                                                                                             |                                                                                       |
| Randomisation                                                                                                                                       | Intervention                                                                                                                                                                                                                                                                                                                                                                                                                                    | Control                                                                               |
| After randomisation                                                                                                                                 | [figure not shown]                                                                                                                                                                                                                                                                                                                                                               |                                                                                       |
| 7-days before appointment, 2-days before appointment and in waiting room prior to appointment.                                                      | [figure not shown]                                                                                                                                                                                                                                                                                                                                                               |                                                                                       |
| Outpatient appointment at RCH                                                                                                                       | [figure not shown]                                                                                                                                                                                                                                                                                                                                                               | [figure not shown]   |
| 1-day after appointment                                                                                                                             | [figure not shown]                                                                                                                                                                                                                                                                                                                                                               | [figure not shown]   |
| 4-weeks after appointment                                                                                                                           | [figure not shown]                                                                                                                                                                                                                                                                                                                                                             | [figure not shown] |
| [figure not shown]                                                                 | Families provided Participant Information Statement and Consent Form (online via REDCap).                                                                                                                                                                                                                                                                                                                                                       |                                                                                       |
| [figure not shown]                                                                 | Families who consent are asked to complete baseline questionnaire directly after completing consent form (online via REDCap).                                                                                                                                                                                                                                                                                                                   |                                                                                       |
| [figure not shown]                                                                 | Families contacted and asked if they are signed up to the RCH patient portal. If they are not signed up to the portal, the study team will help them to sign up.                                                                                                                                                                                                                                                                                |                                                                                       |
| [figure not shown]                                                                 | 7-days before their outpatient appointment they will be reminded to complete the generic P-PROM. If they have still not completed it 2-days before their appointment they will receive another reminder. If they have still not completed it they will receive a reminder in the waiting room directly prior to their appointment to complete the generic P-PROM. They will also be offered the option to complete the generic P-PROM on paper. |                                                                                       |
| [figure not shown]                                                                 | Outpatient appointment at RCH.                                                                                                                                                                                                                                                                                                                                                                                                                  |                                                                                       |
| [figure not shown]                                                                 | Study follow-up questionnaire sent to caregiver and child to assess primary and secondary outcomes. Participants in intervention arm also invited to take part in qualitative interview.                                                                                                                                                                                                                                                        |                                                                                       |

---

### **8.3 Withdrawal of consent - participant withdraws from all trial participation**

Participants are free to withdraw from the trial at any time upon their request or the request of their legally acceptable representative. Withdrawing from the trial will not affect their access to standard treatment or their relationship with the hospital and affiliated health care professionals.

### **8.4 Losses to follow-up**

A participant will be considered lost to follow-up if they fail to complete either the 1-day or 4-week follow-up survey and is unable to be contacted by the trial site staff. The following actions must be taken if a participant fails to return to the clinic for a required trial visit:

- The research team will attempt to contact the participant and counsel the participant on the importance of completing the follow-up surveys and ascertain if the participant wishes to and/or should continue in the trial.
- Before a participant is deemed lost to follow-up, the research team will make every effort to regain contact with the participant (where possible, 3 telephone calls and, if necessary, a certified letter to the participant's last known mailing address or local equivalent methods). These contact attempts will be documented.
- Should the participant continue to be unreachable, they will be considered to have withdrawn from the trial with a primary reason of lost to follow-up.

### **8.5 Replacements**

Participants who have been randomised / assigned trial intervention may NOT be replaced.

### **8.6 Trial Closure**

A participant is considered to have completed the trial if they have completed all phases of the trial including the last survey in the Schedule of Assessments.

The end of the trial is defined as completion of the last survey shown in the Schedule of Assessments in the trial. At this stage, the Sponsor-Investigator will ensure that the HREC/RGO as well as all regulatory and funding bodies have been notified.

## **9 DATA AND INFORMATION MANAGEMENT**

The Principal Investigator is responsible for storing essential trial documents relevant to data management and maintaining a site-specific record of the location(s) of the site's data management-related Essential Documents.

The Principal Investigator is responsible for maintaining adequate and accurate source documents that include all key observations on all participants at their site. Source data will be attributable, legible (including any changes or corrections), contemporaneous, original, accurate, complete, consistent, enduring and available. Changes to source data (hardcopy and electronic) must be traceable, must not obscure the original entry, and must be explained where this is necessary.

The Principal Investigator will be responsible for ensuring that the collected and reported data is accurate, legible, complete, entered in a timely manner and enduring. To maintain the integrity of the data, any changes to data (hardcopy and electronic) must be traceable, must not obscure the original entry, and must be explained where this is necessary.

Any person delegated to collect data, perform data entry or sign for data completeness will be recorded on the delegation log and will be trained to perform these trial-related duties and functions.

The PI has responsibilities in relation to quality management.

The PI will develop SOPs that identify, evaluate and control risk for all aspects of the trial, e.g. trial design, source data management, training, eligibility, informed consent and adverse event reporting.

---

The PI will also implement quality control (QC) procedures, which will include the data entry system and data QC checks. Any missing data or data anomalies will be noted for clarification/resolution.

The PI will monitor and verify that the trial is conducted as stated in the protocol. The Investigator will ensure data are generated, documented (recorded), and reported in compliance with the protocol, good clinical practice and applicable regulatory requirements.

In the event of non-compliance that significantly affects human participant protection or reliability of results, the Sponsor-Investigator will perform a root cause analysis and corrective and preventative action plan (CAPA).

In addition, the site will perform internal quality management of trial conduct, data collection, documentation and completion. An individualised quality management plan will be developed to describe a site's quality management. For example, where data are extracted from an external source such as an Electronic Medical Record (EMR), double data extraction (i.e., multiple researchers will extract data from the same records) will be completed for the first 10% of records to ensure accuracy of data extraction and agreement between researchers extracting data is achieved. If issues are identified, further double data extraction will be conducted.

The following will be completed during data cleaning to ensure quality:

- o Checks for out-of-range values
- o Checks for completeness

## **10 STATISTICAL METHODS**

The study team consulted with the Clinical Epidemiology & Biostatistics Unit (CEBU) at MCRI regarding the design of this trial and statistical methods.

### **10.1 Estimation**

As the study is a pilot trial, we do not require a predetermined number of participants. However, we believe 100 child participants (n=50 in each arm) will give us rich data on the impact of the intervention on the feasibility and acceptability of the intervention. If the intervention is feasible and acceptable the outcome data, which can be collected with minimal burden on participants and resources, will be crucial to inform sample size calculations for fully powered RCTs.

### **10.2 Population to be analysed**

Intention to treat population (ITT): Includes any participant randomised into the trial, regardless of whether they received the intervention.

### **10.3 Handling of missing data**

We will make every attempt to ensure that data are not missing from surveys at the point of completion. If there are missing responses to surveys completed by caregivers and service providers, we will follow up via phone or email to complete the missing responses. If caregivers do not wish to answer any questions, these will remain missing. Additionally, we will describe missingness and consider or explore imputation if no more than 5% missing.

### **10.4 Methods of analysis**

As this is a pilot trial, most analyses are descriptive.

| OUTCOME                                                                                                                                                                                                                            | METHOD OF ANALYSIS                                                                                                                                                                                                                                                                                                                                                                                                               |
|------------------------------------------------------------------------------------------------------------------------------------------------------------------------------------------------------------------------------------|----------------------------------------------------------------------------------------------------------------------------------------------------------------------------------------------------------------------------------------------------------------------------------------------------------------------------------------------------------------------------------------------------------------------------------|
| Acceptability and feasibility.                                                                                                                                                                                                     | 
Most acceptability and feasibility outcomes will be assessed using descriptive statistics.
 
For example, the proportion of patient/caregivers allocated to the intervention arm who completed the PROM will be described.
 
Some sub-group analyses maybe conducted where appropriate by PROM completion type (paper versus portal), appointment type (face to face versus telehealth), and outpatient clinic.
 |
| Discussion of relevant quality-of-life domains in clinical encounter.                                                                                                                                                              | 
Descriptive & inferential statistics.
 
Proportion of patients/caregivers who report discussing quality of life domains that were relevant to them in their most recent clinical encounter. Responses will be compared between participants in intervention and control arm using a chi-squared test.
                                                                                                            |
| Holistic care provided in clinical encounter.                                                                                                                                                                                      | 
Descriptive & inferential statistics.
 
Proportion of patients/caregivers who report discussion of aspects of health beyond just the physical condition they were present for (such as emotional, social, school, hobbies, and spiritual wellbeing) in their most recent clinical encounter. Responses will be compared between participants in intervention and control arm using a chi-squared test.
           |
| Proportion of clinical encounters where a new health problem was detected.                                                                                                                                                         | 
Descriptive & inferential statistics.
 
Proportion of patients where a new health problem was detected in their most recent clinical encounter. Responses will be compared between participants in intervention and control arm using a chi-squared test.
                                                                                                                                                        |
| Proportion of patients who received support (i.e., change medication, referral, connection with support service, connection with online resource) for a health/quality of life problem(s) in their most recent clinical encounter. | 
Descriptive & inferential statistics.
 
Proportion of patients who report receiving support for a health or quality of life problem in their most recent clinical encounter. Responses will be compared between participants in intervention and control arm using a chi-squared test.
                                                                                                                           |
| Patient satisfaction with care in routine outpatient care based on responses to patient satisfaction questionnaire (PSQ).[6]                                                                                                       | 
Descriptive & inferential statistics.
 
The 5 items (ask participants to report on a scale of 0-100) covered by the PSQ for patients will be descriptively assessed, where a mean and standard deviation will be provided for each item. Responses for each item will be compared between participants in intervention and control arm using a t-test.
                                                           |
| Patient - clinician communication. Based on patient/caregiver report to a study designed Likert question in the 1-day follow-up survey                                                                                             | 
Descriptive & inferential statistics.
 
Description of patient's report of patient-clinician communication in their most recent clinical encounter. Responses will be compared between participants in intervention and control arm using a chi-squared test.
                                                                                                                                                    |
| Improvements in child health related quality of life, measured using the CHU9D and based on                                                                                                                                        | 
Descriptive & inferential statistics.
 
The mean difference and standard deviation of CHU9D total score between baseline and 4-week follow-up for participants in intervention
                                                                                                                                                                                                                                   |

| OUTCOME                                              | METHOD OF ANALYSIS                                                                                                                  |
|------------------------------------------------------|-------------------------------------------------------------------------------------------------------------------------------------|
| change between baseline and 4-week follow-up. [7, 8] | and control arm will be reported. Differences between participants in intervention and control arm will be assessed using a t-test. |

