| To determine the impact of a generic paediatric patient reported outcome measure (P-PROM) on patient - clinician communication in routine outpatient care at The Royal Children's Hospital.                  | Patient - clinician communication. Based on patient/caregiver report to a study designed Likert question in the 1-day follow-up survey                                                                                                                                                                                                                      |
| To determine the impact of a generic paediatric patient reported outcome measure (P-PROM) on child quality of life .                                                                                         | Improvements in child health related quality of life, measured using the CHU9D (Appendix B) and based on change between baseline and 4-week follow-up. [7, 8]                                                                                                                                                                                               |

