## 4 TRIAL DESIGN

[figure not shown]

This study is a pilot feasibility and acceptability, non-blinded, randomised control trial (RCT). It is a pilot study because it is the first of its kind to assess a generic P-PROM intervention in routine clinical outpatient care in Australia across a range of clinical contexts and using a generic PROM called the EQ-5D-Y-5L. Hence it is essential to first conduct this pilot study to ensure the intervention is feasible, acceptable and demonstrates some effectiveness in routine clinical care before conducting a full-scale RCT.

A parallel group RCT methodology with an intervention and control arm will be utilised. Participants (children) will be randomly allocated to the intervention and control arm at a 1:1 ratio. An RCT methodology is being employed as it is the gold standard method for assessing the effectiveness of an intervention on an outcome.[9] RCT's balance participant characteristics (both observed and unobserved) between the two study arms, allowing attribution of any differences in outcome to the study intervention, which is not possible with any other study design.[9] An Intention-to-treat (ITT) analysis will be utilised, whereby all participants who are randomized are included in the statistical analysis and analysed according to the group they were originally assigned, regardless of what intervention (if any) they received.

Participants allocated to the intervention arm will receive the study intervention (see details below). Participants allocated to the control arm will receive standard care from their treating clinician at The Royal Children's Hospital at their outpatient clinic appointment.

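### The Likert communication item gets a test that ignores response order, and section 4 asks a pilot sized for no effect to show some effectiveness

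*Protocol*

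**What the plan says.** The communication outcome is defined in the Protocol's summary of objectives and outcomes: "Based on patient/caregiver report to a study designed Likert question in the 1-day follow-up survey". Section 10.4 assigns it the same comparison as the four yes/no outcomes: "Responses will be compared between participants in intervention and control arm using a chi-squared test". For the five patient satisfaction (PSQ) items, scored 0-100, 10.4 says: "Responses for each item will be compared between participants in intervention and control arm using a t-test". Change in CHU9D is also compared by t-test.

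Section 4 explains why a pilot comes first: to ensure that the intervention is feasible, acceptable and "demonstrates some effectiveness in routine clinical care before conducting a full-scale RCT". Section 10.1 says: "As the study is a pilot trial, we do not require a predetermined number of participants", and continues: "we believe 100 child participants (n=50 in each arm) will give us rich data". It adds that the outcome data "will be crucial to inform sample size calculations for fully powered RCTs".

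Section 10.4 also plans arm-level summaries: proportions for the four binary outcomes, a mean and SD for each PSQ item, and the mean CHU9D change with its SD in each arm. It names no between-arm estimate or confidence interval.

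**The concern.** There are two linked problems.

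First, a Likert item is ordered. Pearson chi-squared gives the same result if the response categories are shuffled, so it spreads its power over every possible pattern of difference when the question is whether communication is better or worse. At 50 per arm that loss is large, and recovering it needs no extra data.

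Second, section 4 attaches an effectiveness condition, without a criterion, to a trial whose size was not chosen to show any effect. The only between-arm analyses named for the effectiveness outcomes are significance tests. A reader looking for some effectiveness would have little else to turn to, and could take a non-significant result as absence of effect or a single significant one as proof. Section 10.1 gives planning a later trial as the purpose, and a between-arm difference with its uncertainty serves that better than a p-value.

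**Working it through.** **Inputs.** 50 per arm (section 10.1) and 1:1 allocation (section 4) come from the Protocol. It states no alpha, power, effect size, control rate, SD or number of Likert levels, so there is no planned figure to reproduce. Assumed here: two-sided alpha 0.05; five Likert levels; a proportional-odds shift; control rates 0.10-0.60; standardised differences 0.2-0.8.

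**1. Number of tests in section 10.4.** Chi-squared: relevant domains discussed, holistic care, new problem detected, support received, communication = 5. T-tests: five PSQ items plus CHU9D = 6. Total 5 + 6 = 11.

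**2. Likert item, by simulation.** Control responses are drawn from an assumed distribution. Each cumulative odds is divided by the odds ratio (OR) to give the intervention distribution. Pearson chi-squared and the Wilcoxon rank-sum test are applied to each sample. Three distributions, 2,000 runs each, 50 per arm:

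| Control distribution, lowest to highest (%) | OR 2: chi-squared / Wilcoxon | OR 2.5: chi-squared / Wilcoxon |
|---|---|---|
| 5, 10, 20, 35, 30 | 26% / 47% | 46% / 70% |
| 10, 20, 30, 25, 15 | 30% / 48% | 49% / 70% |
| 2, 3, 10, 35, 50 | 21% / 38% | 38% / 61% |

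A further simulation over four assumed distributions gives 23-30% against 40-48% at OR 2, and 41-50% against 65-72% at OR 2.5. The most skewed row above lies slightly below those ranges, but the gap between the tests has the same size. With no effect, chi-squared rejects in 3.1-4.2% of samples, so it is valid and mildly conservative.

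**3. Sparse cells.** How often an expected count falls below 5 depends on the assumed distribution: from about 6% to over 99% of samples at OR 2. With answers spread evenly, the lowest level has 50 × 0.20 = 10 control responses. In the intervention arm its odds are 0.25/2 = 0.125, a probability of 0.111, or 50 × 0.111 = 5.6 responses. The expected count is (10 + 5.6)/2 = 7.8. With 5% in the lowest level, the odds are 0.0526/2 = 0.0263, a probability of 0.026, and the expected count is (2.5 + 1.3)/2 = 1.9.

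**4. Power of the other tests at 50 per arm.**

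Binary: power = Φ[(d − 1.96·se0)/se1], with se0 = √(p̄(1−p̄)·2/50) and se1 = √((p1(1−p1) + p2(1−p2))/50). For 0.50 against 0.65: se0 = √(0.575 × 0.425 × 0.04) = 0.0989; se1 = √(0.4775/50) = 0.0977; power = Φ[(0.15 − 0.1938)/0.0977] = Φ(−0.448) = 33%.

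Means: power = Φ[δ/√(2/50) − 1.96]. For 0.3 SD: Φ(0.3/0.2 − 1.96) = Φ(−0.46) = 32%.

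| Assumed effect | Power |
|---|---|
| 10 points | 17-29% |
| 15 points | 32-51% |
| 20 points | 52-71% |
| 30 points | 87-95% |
| 0.3 SD | 32% |
| 0.5 SD | 70% |

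Power of 80% needs about 23-28 points (control rates 0.10-0.50), or (1.96 + 0.84) × 0.2 = 0.56 SD. If only 40 per arm were analysed, power would be 27-42% for 15 points and 61% for 0.5 SD.

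**5. Chance findings.** If all 11 null hypotheses were true and the tests independent, the chance of at least one p < 0.05 is 1 − 0.95^11 = 43%. It is lower if the tests are positively correlated, as five items of one questionnaire are likely to be.

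**6. Precision if estimates are reported.** The 95% CI half-width is at most 1.96 × √(2 × 0.25/50) = 0.196, about 20 points, for a risk difference, and 1.96 × √(2/50) = 0.39 SD for a mean difference.

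**The case against.** The strongest reply is that this is an openly labelled pilot. The primary objective is feasibility and acceptability, section 10.4 calls most analyses descriptive, and section 10.1 disclaims a power-based size. Confidence intervals and multiplicity handling commonly belong to a statistical analysis plan, which is not shown here. All of this stands, and it makes the missing intervals and the lack of adjustment weak grounds on their own.

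A reader might infer that effectiveness will be judged by the 11 p-values and the full trial stopped or started on them. The Protocol does not say so: no passage links a p-value, an alpha level or a count of significant results to progression, and section 4 never defines some effectiveness as significance. A reader might also infer that only tests will be reported. In fact arm-level proportions, means and SDs are planned, so control rates and SDs for a later sample size will be available. Nor can power be put at one low value, because it runs from 17% to 95% over the effects tabulated above.

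On the Likert item, it can be said that chi-squared is valid, that this is one item in one secondary outcome, and that chi-squared can detect differences that are not a shift in one direction. That is true, but the objective concerns the impact on communication, which a shift along the scale captures. What remains after these objections is a method that the Protocol itself fixes, and a sentence in section 4 that its sample size does not support.

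**Conclusion.** The point holds in two limited parts.

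The chi-squared test for the Likert item is an inefficient stated choice. An ordinal analysis raises power by roughly 17 to 24 percentage points under the assumptions used (five levels, proportional odds, alpha 0.05, 50 per arm). The direction of the gain is the same for every distribution tried; its exact size, and how sparse the table will be, depend on responses that are not yet known.

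The effectiveness wording in section 4 does not fit section 10.1. The trial is likely to miss small to moderate differences, it would probably detect differences near 30 points, and the 11 tests carry up to about a 43% chance of a false positive if independent. This is a conflict between a stated purpose and an unsized sample. It does not show a faulty decision rule, since the Protocol contains none.

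**What to change.** 1. In section 10.4, replace chi-squared for the communication item with the Wilcoxon rank-sum test, and report a common odds ratio with 95% CI from a proportional-odds model.
2. In section 4, delete the demonstration of some effectiveness as a precondition for a full-scale trial. Rest progression on feasibility and acceptability together, since both form the primary objective; completion and clinician-opening rates alone would leave out acceptability.
3. In section 10.4, or in the statistical analysis plan if one exists, report the other secondary comparisons as between-arm differences with 95% CIs: risk differences for the binary outcomes and mean differences for the PSQ items and CHU9D change. Item-level PSQ reporting can stay as planned; nothing in the Protocol calls for a single score.

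The data collected do not change. The cost is table wording in 10.4 and one sentence in section 4. The downside is that the pilot will have no p-value headline on effectiveness.
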